### Intervention description

Group B (Interventional group) –
*Rasonapinda*
^
12
^ 500 mg twice a day with water

Ingredients of
*Rasonapinda* are
*Allium sativum (Rasona 72 gm), Ferula asafetida (Hingu 12 gm), Cuminum cyminum (Jeeraka 12 gm), Sodiichloridum (Saindhavlavana and Souvarchalalavana 12 gm each), zingiber officinale (Shunthi 12 gm), Piper nigrum (Maricha 12 gm), Piper longum (Pippali 12gm), Ricinus communis (Eranda- Quantity sufficient).*

**Group A**
 (Controlled group) –
*Trayodashang guggul*
^
13
^
^,^
^
14
^ 500 mg twice a day with water

Ingredients of
*Trayodashang guggul* are 13 parts
*Commiphoramukul (Guggul),* 1 part of each
*-Acasia Arabica (Aabha), Withaniasomnifera (Ashwagandha), Juniperus communis (Harpusha), Tinospora cordifolia (Guduchi), Asparagus recemosus (Shatavari), Tribulus terresteris (Gokshur), Argyria speciosa (Vriddhadaru), Pluchea lanceolata (Rasna), Foeniculumvalgare (Shatapushpa), Curcuma zedoaria (Karchur), Trachhyspermumammi (Yavani), Zingiber officinale (Shunthi),* 1/2 part of
*Clarified butter (Ghrut).*

**Adjuvent Therapy**

*– katibasti* (oil pooling therapy) with
*Dashmoola* oil

**
*Dashmoola oil*
** literally means oil prepared of 10 roots of medicinal herb is a polyherbal preparation pacifying all three bodily humours (
*vata, pitta* and
*kapha*), more specifically having
*vata* pacifying effect mentioned in bhaishajyaratnavali under the management of brain disorders (
*Shirorogadhikar*). It is a well-known for alleviating
*Vata* type of bodily humour by oleation therapy.
^
15
^

Ingredients of
*Dashmool* oil are 1 part each of roots of
*Aegle marmelos (Bilwa), Premna serratifolia (Agnimantha), Oroxylum indicum (Shyonak), Stereospermum suaveolance (Patala), Gmelina arborea (Gambhari), Desmodiumgangeticum (Shalaparni), Uraria picta (*Prishniparni),
*Solanum indicum (Brihati), Solanum surattense (Kantakari), Tribulus terrestris (Gokshura), Vitex negundo (Nirgundi), Brassica comprestris (Sarshap).*

### Drug preparation

*Rasonapinda* will be prepared according to the standard operating procedures outlined in
*Sharangdhar Samhita- Madhyam Khand* (ayurveda classics).

*Rasonapinda* will be prepared according to modified form by giving three bhavanas (triturations) of erandmool decoction and converting it into tablet form for easy acceptability and convenience to the patient and further standardization of
*Rasona Pinda* will be done.
^
16
^

### Procedure of Rasona Pinda preparation

Fine powder of all ingredients-
*Allium sativum (Rasona 72 gm), Ferula asafetida (Hingu 12 gm), Cuminum cyminum (Jeeraka 12 gm), Sodiichloridum (Saindhavlavana and Souvarchalalavana 12 gm each), zingiber officinale (Shunthi 12 gm), Piper nigrum (Maricha 12 gm), Piper longum (Pippali 12 gm)* will be taken and mixed thoroughly. To this powder, ricinus communis root (erandmool) decoction will be added and triturated for three hours. Such three triturations (
*bhavanas*) will be given. After drying granules will be prepared and tablet of each 250 mg will be prepared by tablet punching machine.

*Trayodashang Guggul* and Dashmool Taila will be procured from a pharmaceutical company.

### Intervention modification

Any unfavourable effects during the course of the treatment will be observed and will be reported to the ethical committee. The patients’ unpleasant effects will be taken care of. Any withdrawal requests from participants will be addressed along with the justification for ending the course of therapy.

### Outcomes

To compare efficacy of
*Rasonapinda* and
*Trayodashang guggul* as an adjuvant to
*katibasti* (oil pooling therapy) in subjective and objective parameters.

### Assessment criteria

Assessment will be done on 0
^th^, 15
^th^, 30
^th^ day during treatment and 45
^th^ day after treatment

### Subjective criteria – Gradation
^
17
^

*Ruk* (pain)

*Stambha* (stiffness)

*Toda* (pricking pain)

*Muhuspandana* (numbness)

*Aruchi* (anorexia)

*Tandra* (drowsiness)

Functional disability – Oswestry Disability Assessment Questionnaire

### Objective criteria – (before and after)

SLRT (Straight Leg Raising test)

Walking time – to cover 25 meters

Schober’s Test

Bowstring test

### Oswestry Low Back Pain Disability Questionnaire
^
18
^

Questionnaire description: Each of the 10 sections that describe the pain and its effects is evaluated from 0 to 5, with higher values indicating a more severe impact.

*Schober’s test*

Locate L5 spinous process (level of posterior superior illiac spine, dimpuls of venus).

Mark 5 cm below and 10 cm above.

Requesting the patient to touch their toes.

Measure the space between the marks.

Normal > 5 cm, Abnormal< 2.5 cm

*Bowstring test*

Subject is supine.

Passively perform SLR on the involved side, if the pain is experienced, flex the subject’s knee to 20 degrees in attempt to reduce the pain.

After that, exert pressure there in an effort to simulate radicular pain.

(+) Tension on the sciatic nerve is indicated by painful radicular reproduction after popliteal compression.

### Participant timeline

Patients will be treated for 30 days and assessment will be done up to 45 days as mentioned in
Figure 1.

**Figure 1. f1:**
[figure not shown]
CONSORT flow diagram showing study timeline.

### Recruitment

As per sample size calculation, total patients will be recruited. Data collected will be analyzed by using appropriate statistical methods. The patients of
*Grudhrasi* will be selected from the Kayachikitsa Out-patient department and In-patient department of Mahatma Gandhi Ayurved College, Hospital & Research Centre, Salod (H), and from specialized peripheral camps.

**
*Enrolment and interventions time schedule*
**

The intervention period will be from 0 to 30 days and follow up on the 0
^th^, 15
^th^, 30
^th^ and 45
^th^ day.

**
*Sample size*
**

Formula using Mean difference:

$$n1=n2=2\frac{{\left(Z_{\alpha }+Z_{\beta }\right)}^{2}\sigma^{2}}{{\left(\delta \right)}^{2}}$$

$Z_{\alpha }=1.96$

α=Type I error at 5% at both sides two tailed

$Z_{\beta }=0.84=\text{Power at 80\%}$

Primary Variable = Radiation of Pain

(Mean) value of Radiation of Pain for Trayodashangguggul treatment group (Before) = 2.27 (As per reference article).
^
19
^

(Mean) value of Radiation of Pain for Trayodashangguggul treatment group (After) = 0.93.

Mean Difference for the effect in Trayodashangguggul after and before 2.27 – 0.93 = 1.34.

Standard Deviation = 0.62

Considering 20% clinically relevant margin for RasonaPinda

$\left(\delta \right)$
 = (1.34 *35) /100 = 0.469.

Sample size N =

$n1=n2=2\frac{{\left(1.96+0.84\right)}^{2}{\left(0.62\right)}^{2}}{{\left(0.469\;\right)}^{2}}=28\;\text{per group}$

Considering 10% drop out = 2

Total sample size required = 28 + 2 = 30 per group.

A total of 60 patients will be recruited for the study.

**Allocation sequence generation** – Computer-Generated Randomization.

**Concealment of allocation** – assessor blinding.

**Allocation implementation** – the first author will generate an allocation sequence, enrol participants, and assign participants to intervention.

**Blinding –** randomized single blind standard controlled superiority clinical trial.

The outcome assessor will be blinded.

Unblinding will not be permissible to outcome assessor.

Participant will be revealed about allocation of intervention at the time of enrolment.

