### Ethical considerations

The ethical clearance for the publication of this protocol was taken from the I.E.C. committee at Mahatma Gandhi Ayurveda College, Hospital and Research Centre Salod (H), Wardha, Datta Meghe Institute of Medical Sciences with Ref No.-MGACHRC/IEC/july-2022/549 (11/08/22).

CTRI registration for this study – CTRI/2022/12/048534 (27/12/2022).

The committee will decide on the endpoint and oversee the trial as it progresses.

The researcher will assess any adverse event and these will be reported to the ethics committee.

**Consent –** The recruitment of the patient in study groups will be done with written informed consent in their local language while explaining every aspect of the study by the researcher.

Before, during, and after the experiment, the participants’ personal data will be gathered and kept private. The researcher will be the only one having access to the physical data storage facility. Computerised information will be kept on a hard drive that is password-protected and only the researcher can access it.

**Inclusion criteria –** Patients willing to participate with written informed consent.

Patients aged between 20–60 yrs.

Patients having classical sign and symptoms of
*Grudhrasi Ruk* (pain),
*Stambha* (stiffness),
*Toda* (pricking pain),
*Muhuspandana* (numbness),
*Aruchi* (anorexia),
*Tandra* (drowsiness).

Patient fulfilling diagnostic criteria like positive SLRT, Schober’s test, Bowstring Test.

**Exclusion criteria –** Cases of traumatic injury.

Known cases of bone tumour, cancer of spine, tuberculosis of vertebral column, fibrosis of sacral ligaments, and protruded inter vertebral disc except lumbar spondylosis.

Patients with serious health issues such as diabetes mellitus, heart disease, kidney disease, cancer, tuberculosis, and other systemic disorders.

Pregnant and lactating women.

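### The sample size rests on a primary variable, radiation of pain, that matches no outcome on the assessment list, and no primary visit is named

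*Protocol article*

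**What the plan says.** All references are to the protocol article.

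- **Recruitment, Sample size:** "Primary Variable = Radiation of Pain". The inputs are a before/after change under the control drug ("Mean Difference for the effect in Trayodashangguggul after and before 2.27 – 0.93 = 1.34"), "Standard Deviation = 0.62", a two-sided 5% level and 80% power. The result is 28 per group, raised to 30 for dropout.
- **Subjective criteria:** six symptom grades (Ruk or pain, stiffness, pricking pain, numbness, anorexia, drowsiness), then "Functional disability – Oswestry Disability Assessment Questionnaire". That makes seven outcomes.
- **Objective criteria:** straight leg raising, time to walk 25 m, Schober's test and the bowstring test. That makes four. The heading describes them as measured before and after.
- **Outcomes:** one sentence on comparing efficacy, ending "oil pooling therapy) in subjective and objective parameters". It names no primary outcome.
- **Study setting and Data collection plan:** all parameters are recorded on days 0, 15, 30 and 45, according to the subjective and objective criteria.
- **Statistical methods:** the primary outcome is analysed by paired tests within groups and by a t-test or Mann-Whitney test of change between groups. Neither the outcome nor the visit is named.
- **Ethical considerations:** "The committee will decide on the endpoint and oversee the trial as it progresses".
- **Study status:** recruitment has started.

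**The concern.** Two stated parts of the plan do not fit together. One names the variable that justifies 60 patients. The other lists what will be assessed, and the named variable is not on it. An analysis plan written later could choose a visit, but it could not recover a baseline grade that was never taken.

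Two things are at stake. The first is power: the effect size and SD come from radiation of pain, and the article gives no SD for any of the 11 listed outcomes, so the 80% cannot be carried over to one of them. The second is the error rate: a primary analysis not tied to a recorded outcome and visit can be attached to whichever comparison looks best. The Data collection plan adds to this by treating improvement on the assessment criteria generally as the mark of significance.

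**Working it through.** **1. The plan's own figure.** Inputs from the Sample size section: Zα = 1.96, Zβ = 0.84, σ = 0.62, δ = 0.35 × 1.34 = 0.469.

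n = 2 × (1.96 + 0.84)² × 0.62² / 0.469² = 2 × 7.84 × 0.3844 / 0.21996 = 27.4, rounded up to 28 per group.

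The stated 28 reproduces. (The text beside δ speaks of a 20% margin while the arithmetic uses 35%. That is a separate matter and plays no part here.)

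**2. Matching the sizing variable to the assessment list.** The nearest of the 11 entries is Ruk, glossed only as pain. The article does not say that Ruk is the radiation item, gives no grading scale for it, and does not tie 2.27, 0.93 or 0.62 to it. The Background of the Abstract lists piercing pain and pain radiating from the lumbosacral region as separate symptoms.

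**3. Candidate between-group comparisons if the primary is not fixed.**
- One visit: 7 + 4 = 11.
- All parameters at three post-baseline visits (Study setting): 11 × 3 = 33.
- Objective tests compared once only, as their heading suggests: 7 × 3 + 4 = 25.

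**4. Chance of at least one false positive, each test at 5%.** Under independence this is 1 − 0.95^k.

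| k | Chance |
|---|---|
| 11 | 1 − 0.95^11 = 0.431 |
| 25 | 1 − 0.95^25 = 0.723 |
| 33 | 1 − 0.95^33 = 0.816 |

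Outcomes and visits in the same patients will be correlated, and the article gives no correlations. The next table assumes one common correlation among normal test statistics (simulation, 100,000 draws, two-sided cut-off 1.96).

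| Assumed correlation | 11 tests | 33 tests |
|---|---|---|
| 0.3 | 0.38 | 0.69 |
| 0.5 | 0.30 | 0.53 |
| 0.7 | 0.22 | 0.35 |
| 0.9 | 0.13 | 0.18 |

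Every entry is above 0.05. All of them presuppose a free choice after the data are seen.

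**The case against.** Three stronger conclusions are tempting, and the article does not support them.

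*The variable behind the sample size will not be collected.* The Introduction describes the condition as pain-dominant, with pain radiating down the leg, so Ruk may be the item meant. The grading is given only by citation and the case record form is not reproduced, as is usual in a journal article. What stands is narrower: no listed outcome has the name, and no statement links the two.

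*A committee will pick the endpoint during the trial.* The sentence appears among oversight and adverse-event provisions. Its closing words attach most naturally to overseeing, and endpoint may mean when the trial ends. Choosing the primary outcome mid-trial is a possible reading, but not the only one. The finding does not depend on it.

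*The confirmatory test is undefined, and the error rate is 82%.* Statistical methods does give a between-group test of change and separates primary from secondary outcomes. The before/after sizing contrast and the 30-day treatment hint at day 30. Nothing says that any significant result will count as success, and if one primary comparison is honoured its 5% level holds. What is missing is the recorded outcome and the visit to which the test belongs.

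It can also be said that an analysis plan not shown may settle the matter. That would answer an omission. Here the article states a primary variable and an assessment list, and the two do not match.

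**Conclusion.** The point holds as a mismatch that must be resolved. The trial is sized on radiation of pain, no listed outcome is identified with it, the Outcomes section names no primary outcome, and no visit is chosen among days 15, 30 and 45. The arithmetic of 28 per group is sound for the inputs used, but the 80% power is tied to no outcome that the plan says it will record.

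The error rates are illustrations, not properties of the plan. They apply only if the choice stays open until data are seen: 43% for 11 independent tests, 72% for 25 and 82% for 33, or about 18–69% for 33 tests at assumed correlations from 0.9 down to 0.3. That radiation of pain goes unmeasured, or that a committee will select the endpoint from accruing data, is something a reader might infer but the article does not establish.

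**What to change.** 1. Settle the primary variable in one of two ways. Either add a graded radiation-of-pain item to the assessment list, on the scale that gave 2.27 and 0.93, or state that a listed outcome (for example the Ruk grade or the Oswestry score) is the primary variable. In the second case, restate the sample size or power with that outcome's own SD.
2. Name the change from baseline to one visit, for example day 30 at the end of treatment, compared between groups, as the single primary analysis. Make all other outcomes and visits secondary.
3. Reword the sentence in Ethical considerations so that it is clear that the committee does not choose the primary endpoint after recruitment has begun. It should be clarified rather than deleted, since it may carry an oversight provision.

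Splitting the 5% level across outcomes is a poor substitute. Even if δ = 0.469 and SD 0.62 applied to every outcome, Bonferroni over 11 tests (level 0.0045) would leave 28 per group with about 50% power.

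The cost is a protocol and registry amendment and, if an item is added, one more line on the case record form. Patients already enrolled may lack that item at baseline and must be counted and reported, so the cost grows with each further enrolment.

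### The sample size names a 20% relevant margin but computes delta from 35%; for the 20% margin, 28 per group gives about 36% power, not 80%.

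*Protocol article*

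**What the plan says.** The calculation is printed in full in the protocol article, Recruitment section, under Sample size. It uses the usual formula for comparing two means, with a two-sided 5% test ("α=Type I error at 5% at both sides two tailed") and 80% power. The variable is named as "Primary Variable = Radiation of Pain". The reference effect comes from a cited study of the control treatment: "Mean Difference for the effect in Trayodashangguggul after and before 2.27 – 0.93 = 1.34". The spread is given as "Standard Deviation = 0.62".

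The target difference is introduced with "Considering 20% clinically relevant margin for RasonaPinda". The line that follows computes it as "1.34 *35) /100 = 0.469". That value enters the formula and gives 28 per group. The dropout step reads "Considering 10% drop out = 2", which brings the total to 30 per group and 60 overall. The Study setting section and the blinding entry both describe a superiority trial.

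**The concern.** Two adjacent lines give different percentages for the same quantity, and nothing else in the article explains the 35% or reconciles it with the 20%. This is not an effect of condensing a longer document, because every step of the calculation is shown and two of the steps conflict.

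This calculation is the only justification for 60 patients. If 20% is the difference regarded as clinically relevant, the 80% power belongs to an effect 1.75 times as large (0.469 / 0.268), and a true 20% advantage would be missed about two times in three. The comparator is an active treatment, so a non-significant result is quite possible. Readers who rely on the stated margin and power could then take it as evidence against a relevant difference, which the trial could not supply.

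**Working it through.** **Inputs**, all from the Sample size part of the Recruitment section: Zα = 1.96, Zβ = 0.84, SD σ = 0.62, control change 2.27 − 0.93 = 1.34, equal groups, 10% dropout.

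**1. The plan's own figure.** n per group = 2(Zα + Zβ)²σ²/δ².
With δ = 0.35 × 1.34 = 0.469: 2 × 2.80² × 0.62² / 0.469² = 27.4, so 28. The printed figure is reproduced.

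**2. The margin stated in words.** δ = 0.20 × 1.34 = 0.268.
n = 2 × 2.80² × 0.62² / 0.268² = 83.9, so 84 per group (85 with unrounded Z values or the t-test). Allowing for 10% loss, 84/0.9 = 93.3, so 94 per group.

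**3. Power.** By the normal approximation, power = Φ(δ / (σ√(2/n)) − 1.96).
For n = 28, σ√(2/n) = 0.62 × 0.2673 = 0.1657.
- δ = 0.268: 0.268/0.1657 − 1.96 = −0.343, power 36.6%.
- δ = 0.469: 0.469/0.1657 − 1.96 = 0.870, power 80.8%.

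The noncentral t distribution gives slightly lower values:

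| Evaluable per group | Power at δ = 0.268 (t / normal) | Power at δ = 0.469 (t / normal) |
|---|---|---|
| 27 | 34.4% / 35.5% | 77.9% / 79.4% |
| 28 | 35.5% / 36.6% | 79.4% / 80.8% |
| 30 | 37.7% / 38.8% | 82.1% / 83.4% |

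**4. Other explanations for the gap.**
- A one-sided 5% test at δ = 0.268 gives 48.9% power with 28 per group and needs 67 per group, so sidedness does not explain it.
- Taking 20% of the baseline mean gives 0.20 × 2.27 = 0.454, which is not the printed 0.469 and would need 30 per group before dropout.

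**5. What the 35% effect means.** If the control group ends at 0.93, Rasonapinda must end at 0.93 − 0.469 = 0.461, about half the residual grade. A 20% effect would end at 0.93 − 0.268 = 0.662.

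**6. Dropout.** Ten percent of 28 is 2.8, yet 2 are added. To keep 28 evaluable, 28/0.9 = 31.1, so 32 per group. Thirty per group with 10% loss leaves 30 × 0.9 = 27.

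**7. Precision.** With 27 per group and SD 0.62, the expected half-width of the 95% confidence interval for the difference is about 2.007 × 0.62 × √(2/27) = 0.34 grade. This is wider than 0.268, so an estimate of zero could not exclude a 20% difference.

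**The case against.** The strongest reply is that the 20% may be a stale or mistyped figure. It appears once, in words, while the multiplier, the 0.469, its substitution in the formula and the 28 all agree with one another. On that reading 28 per group is right for 80% power, and 0.268 has no standing as a benchmark. This stands as a possibility, since the article does not show which figure was intended. It does not remove the error: the plan would then misstate its clinically relevant margin and leave the 35% unexplained. The 36% figure is conditional on the margin as stated.

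Three smaller objections have some force.
- The dropout shortfall is minor. Going from 28 to 27 evaluable costs about 1.5 points of power, and 27.4 plus 10% is 30.1, close to the 30 used. It is a side point.
- No passage says that a non-significant result will be read as no difference. That risk is a judgement about later reporting and not a statement in the plan.
- The article does not say whether 0.62 is the SD of the baseline score, the final score or the change, whereas the Statistical methods section compares changes between groups. The power figures therefore assume that 0.62 is the SD of the quantity tested. For 28 per group to give 80% power at 0.268, the SD would have to be 0.268 / (2.80 × 0.2673) = 0.36, far below 0.62. A larger SD would lower the power at both margins.

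**Conclusion.** The concern holds. The stated margin and the delta used contradict each other, and the sample size supports only the latter. Taking SD 0.62, a two-sided 5% test and equal groups as the protocol gives them, 28 per group has 35.5% to 36.6% power for the 20% margin (0.268) and 79.4% to 80.8% for 35% (0.469). If 20% was meant, the trial has about one third of the 84 per group required. If 35% was meant, the number stands, but the plan describes its target wrongly and is powered only for roughly halving the residual grade left by the control treatment. Either way the text must be corrected. The dropout step adds a small further shortfall, to 27 evaluable per group against the 28 required.

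**What to change.** First state which percentage was intended and give the reason for it. The Study status section says recruitment has begun, so this should be settled before outcome data are examined.

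Then report what 60 patients deliver, for example:

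> Delta is 35% of 1.34, that is 0.469 grade. With 27 evaluable patients per group after 10% loss, power is about 78% (two-sided 5%, SD 0.62). For a 20% difference (0.268 grade) power is about 35%.

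Remove the 20%, or label it as a margin for which the trial is not powered. State which SD the 0.62 is. Add that a non-significant result will be interpreted through the 95% confidence interval for the difference and not as equivalence. The interval should be read against 0.268 as long as 20% is regarded as clinically relevant; if that figure is withdrawn as an error, name and justify the relevant difference that replaces it.

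The cost is a change of protocol wording. The stated power becomes less favourable, and no extra patients are needed.

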**Methods:**

In this study, a total of 60 patients will be enrolled and divided equally into two groups. In group A,
*Trayodashang Guggul* 500 mg twice a day after meal with warm water for 30 days adjuvant with katibasti for the initial 7 days will be given. In group B,
*Rasonapinda* 500 mg twice a day after meal with warm water adjuvant with katibasti for the initial 7 days will be given for 30 days.

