## Methods

### Study setting

The patients will be selected from OPD and IPD of department of kayachikitsa of the Mahatma Gandhi Ayurved College, Hospital & Research Centre, Salod (H) and peripheral camps, mainly the population of Wardha district including patients of all community, (Maharashtra) India. A total of 60 patients will be recruited for the study. They will randomly be divided into two groups; Group A (controlled group) –
*Trayodashang Guggul*, and Group B (interventional group) –
*Rasona Pinda*. All the baseline parameters will be recorded at the start of the study. The patients will undergo treatment for 30 days for both groups. All the parameters will be recorded at the 0
^th^, 15
^th^, 30
^th^, 45
^th^ day of the study duration.

**Sample size:** 60 (including sample size calculation).

**Grouping:** Group A (controlled group) – (n=30)
*Trayodashang Guggul* as an adjuvant to
*katibasti* (oil pooling therapy).

Group B (Interventional group) – (n=30)
*Rasonapinda* as an adjuvant to
*katibasti* (oil pooling therapy).

All the baseline parameters will be recorded at the beginning of the study. The patients will undergo treatment for 30 days in both groups. Follow ups will be taken on the 15
^th^ and 30
^th^ days during treatment and the 45
^th^ day after treatment.

**Guidelines:** The SPIRIT guidelines were used for the study protocol.
^
11
^

**Case definition:** Patients between 20–60 years of either sex having classical signs and symptoms of
*Grudhrasi* (sciatica) willing to give written informed consent.

**Sampling procedure:** Simple random sampling by computerized table method.

**Type of study:** Interventional study.

**Study design:** Randomized standard controlled single-blind superiority clinical trial.

Simple randomization method will be used to allocate participants in controlled and interventional group. A Random number generator will be used and unique number is given to each participant. Participant with even number will be allocated in controlled group and participant with odd number will be allocated in Interventional group.

**Data monitoring:** formal committee.

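### Assessor blinding is given as the allocation concealment while one person generates the sequence, enrols and assigns, so nothing stated stops the enroller from knowing the next arm

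*Protocol article*

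**What the plan says.** The Recruitment section of the protocol article deals with allocation in consecutive lines:

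- Sequence generation: "Computer-Generated Randomization".
- Concealment: "Concealment of allocation – assessor blinding".
- Implementation: "the first author will generate an allocation sequence, enrol participants, and assign participants to intervention".
- Blinding: "The outcome assessor will be blinded", and "Participant will be revealed about allocation of intervention at the time of enrolment".

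The Study setting section adds the method and the coding. "Simple randomization method will be used to allocate participants in controlled and interventional group". A random number generator is used, each participant receives a unique number, and "Participant with even number will be allocated in controlled group and participant with odd number will be allocated in Interventional group".

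On group sizes, the abstract says that "a total of 60 patients will be enrolled and divided equally into two groups". Study setting and Table 1 both give 30 per group. The Study status paragraph says that recruitment has begun.

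**The concern.** Concealment and blinding protect against different things. Concealment keeps the coming assignment from whoever decides whether a patient enters the trial, up to the moment that decision is final. Assessor blinding keeps the arm from whoever measures the outcome, after assignment. The article puts the second where the first belongs, and gives one person the three tasks that concealment is meant to separate.

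What is at stake is whether the two groups are comparable. Entry depends partly on clinical judgement of symptoms such as pain, stiffness and pricking pain. Patients come from outpatient and inpatient clinics and from peripheral camps. An enroller who knows the next arm has room to defer, favour or discourage a patient, knowingly or not. A blinded assessor would then measure accurately a difference that arose at entry.

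**Working it through.** **1. The stated steps in order of time.**

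| Step | Who | Is the next arm hidden from the enroller? |
|---|---|---|
| Generate sequence | first author | No: the enroller makes it |
| Judge eligibility, take consent, enrol | first author | No barrier stated |
| Assign arm by parity of number | first author | No: even or odd gives the arm |
| Tell participant the arm | at enrolment | Not placed after a recorded, final enrolment |
| Measure outcome | blinded assessor | Too late to matter for entry |

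The only protective measure is in the last row. Two ways of working fit the text. If the list is made in advance, the enroller has it. If a number is drawn for each patient, the enroller can see the draw before committing the patient. Neither conceals the allocation. The article mentions no envelopes, no centrally or pharmacy-held list and no independent custodian.

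**2. The plan's own sample size, for reference.** Inputs from the Sample size paragraph: Z values 1.96 and 0.84, SD 0.62, delta 0.469.

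n per group = 2 × (1.96 + 0.84)² × 0.62² / 0.469² = 2 × 7.84 × 0.3844 / 0.21996 = 27.4, rounded up to 28.

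The stated 28 reproduces. Concealing the allocation would not change it.

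**3. Scale of possible harm (assumed shifts, not estimates).** The document gives no basis for the size of any selection effect. Suppose there is no true treatment effect, 28 patients per arm are analysed, and selection alone separates the arms by s standard deviations. With nc = s / √(2/28), the two-sided error rate is 1 − Φ(1.96 − nc) + Φ(−1.96 − nc).

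| Assumed s | Points at SD 0.62 | Error rate (nominal 5%) |
|---|---|---|
| 0.1 | 0.06 | 7% |
| 0.2 | 0.12 | 12% |
| 0.3 | 0.19 | 20% |
| 0.5 | 0.31 | 46% |

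The table shows only how sensitive a trial of this size is. It does not say which row applies.

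**4. Group sizes under simple randomisation.** If the 60 draws are independent with probability 0.5:

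- P(exactly 30/30) = C(60,30) / 2⁶⁰ = 0.103
- P(27:33 or more uneven) = 0.519
- P(25:35 or more uneven) = 0.245

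The cost in power is Φ(0.469 / (0.62 × √(1/n₁ + 1/n₂)) − 1.96):

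- 30:30: Φ(2.930 − 1.96) = 83.4%
- 25:35: Φ(2.889 − 1.96) = 82.3%

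With 56 evaluable patients, an even split gives 80.8% and a split in the ratio 25:35 gives 79.7%. Either way the loss is about one point.

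**The case against.** A condensed article may leave detail to a fuller protocol. That does not help here, because nothing has been left out: the concealment entry is filled in with a different concept, and the three roles are expressly given to one person. A fuller document with real concealment would contradict this text.

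Other objections are stronger, and they limit the point.

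- **Timing.** The article does not say when a number is drawn or seen. A reader might infer that every one of the 60 allocations is known beforehand. The text supports less: the arm can be known, and nothing prevents it.
- **The odd/even rule.** A reader might take it for alternation by order of arrival. It is tied to a random number generator, and parity of a random number is a valid way to code simple randomisation. It matters only because a visible number reveals the arm.
- **Direction.** A reader might infer that milder patients would be steered to *Rasonapinda* and flatter it. The between-group primary analysis compares changes from baseline, and milder patients have less room to improve, so such steering could work against it.
- **Adjustment.** The Statistical methods paragraph plans regression for potential confounders. That would partly correct imbalance in measured severity, but not selection on what is unmeasured.
- **Equal groups.** A reader might infer that the stated method cannot give 30/30. If the unique numbers are 1 to 60 in random order, parity gives exactly 30/30. The range of numbers is not stated, so the binomial figures rest on independent draws.

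**Conclusion.** The point stands on the article's own wording. Concealment is mis-specified as assessor blinding, and one person generates, enrols and assigns, so the stated procedure leaves selection bias open. This should be corrected before further patients are allocated, because an allocation made without concealment cannot be redone.

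The document shows an open route to bias. It does not show that bias has occurred, in which direction it would run, or how large it would be. The error rates of 7% to 46% rest wholly on assumed shifts of 0.1 to 0.5 SD. Computer generation of the sequence is sound; the defect lies in concealment and implementation.

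The group-size point is secondary. Simple randomisation does not by itself guarantee 30 per group, but the consequence for power is about one percentage point even at 25:35.

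**What to change.** For all remaining patients:

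1. Have an existing staff member with no role in enrolment or outcome assessment generate and hold the sequence.
2. Release each assignment only after consent, eligibility and Day-0 assessments are recorded. Sequentially numbered opaque sealed envelopes would do at the hospital; release by telephone would suit the peripheral camps.
3. Replace the concealment entry in the Recruitment section with this procedure, and list assessor blinding under blinding only.
4. Document the procedure used so far, and report how many patients were allocated before the change.
5. For group sizes, either use a restricted 1:1 list with randomly varied block sizes, or describe 30 per group as the expected number.

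The cost is a short amendment and a little of an existing colleague's time. The sample size does not change.
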